### Objectives and hypotheses of the study

The primary objective of the present study is to assess the impact of 8-week vitamin D_3_ and omega-3 fatty acids co-supplementation on serum 25(OH)D, inflammatory biomarkers, CRP/albumin, tumor marker CEA, body mass index (BMI), and body composition in patients with stage ӀӀ or ӀӀӀ CRC undergoing chemotherapy. As a second objective, the study will also evaluate the relationship between alterations in 25(OH)D levels and other variables. It is also expected that there will be improvement in evaluated variables.

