### Measurements

A questionnaire about patients’ medications, diseases, cancer history, and probable supplement use will be recorded at the beginning of the intervention. Dietary intake will be evaluated by 3-day, 24-h record questionnaires (two week days and one weekend day) at baseline and the end of the intervention, and total energy, macronutrient, and some micronutrient (vitamins A, D, E; calcium and selenium) intake will be estimated using nutritionist IV software. To evaluate physical activity levels the short form of the international physical activity questionnaire (IPAQ) [27] will be used at baseline and the end of the intervention. Sun exposure will be assessed with the questionnaire [28] at baseline and the end of the study. A sunshine exposure score is obtained based on (a) how often and what time of day the subjects are outside, (b) which parts of the body are exposed as a percentage of total body surface area, and (c) do the subjects use sun screen or not. Anthropometric indices will be measured after overnight fasting, with minimal clothing and without shoes, before and after the intervention. Body weight will be measured to an accuracy of 0.1 kg using a Beurer scale (Beurer, Germany). Height will be assessed to the nearest 0.5 cm in the standing position without shoes. BMI will be computed as body weight (kg) divided by height squared (cm^2^). A bioelectric impedance analyzer (Quad scan 4000; Body stat) will be used to measure total body fat and fat free mass percentage. The difference in CRP/albumin levels, as an indicator of nutritional status, between groups will also be compared with score values proposed by Correa et al.: no risk ≤ 0.4; low risk = 0.4–1.2; medium risk = 1.2–2; high risk ≥ 2.0 [29]. This indicator will be assessed at baseline and end of the intervention.

Before and after the intervention, blood samples will be collected after 12-h overnight fasting. The serum of patients will be kept at − 80 °C until biochemical analyses. Serum 25(OH)D will be measured by enzyme-linked immunosorbent assay (ELISA) and Euro Immun kit (Euro Immun, Germany). Serum TNF-α, IL-1β, IL-6, and IL-8 levels will be assessed by ELISA and Bender Med kit (Bender Med, Germany). Serum CRP and albumin will be determined by ELISA and Binding kit (Binding, UK). Tumor marker CEA will be evaluated by ELISA and CanAg kit (CanAg, Italy).

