### Statistical analysis

All analyses will be performed with STATA statistics software, version 11.0 (STATA Corporation, College Station, EUA). Kolmogorov-Smirnov test will be used to assess normality of data. Quantitative and normally distributed parameters will be expressed as mean + standard deviation. Quantitative and non-normally distributed data will be shown as median and interquartiles. Analysis of variance (ANOVA) test will be used for comparing the values between and within groups. Analysis of covariance (ANCOVA) will be used to identify any differences between the four groups at the end of study, adjusting for baseline values and covariates (such as dietary intake, physical activity, and sun exposure). Bonferroni will be used to pairwise comparisons for the values after the intervention.

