### Trial status

This trial is in the enrolment stage.

Protocol version 4, 5/4/2019.

Date recruitment began on 4/30/2018.

Recruitment will be completed on 5/15/2019.

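### Calendar season is not among the named ANCOVA covariates for serum 25(OH)D, although recruitment spans every season and the sun score as described has no time-of-year item: a minor, nearly free gain in precision

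*Protocol article*

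**What the plan says.** The primary objective concerns the effect of "omega-3 fatty acids co-supplementation on serum 25(OH)D, inflammatory biomarkers, CRP/albumin, tumor marker CEA" and body measures, so serum 25(OH)D is its first-named outcome. The second objective relates change in 25(OH)D to the other variables.

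On the analysis, the protocol article plans a four-arm ANCOVA of the final values, "adjusting for baseline values and covariates (such as dietary intake, physical activity, and sun exposure". For the contrasts between arms it adds: "Bonferroni will be used to pairwise comparisons for the values after the intervention".

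The Measurements section describes the sun covariate: "A sunshine exposure score is obtained based on (a) how often and what time of day the subjects are outside", then the body parts exposed and the use of sunscreen. It is taken at baseline and at the end of the study.

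The Trial status section gives the calendar: "Date recruitment began on 4/30/2018" and "Recruitment will be completed on 5/15/2019". The Randomization and blinding section states computer-generated allocation to four groups and mentions no stratification by date.

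**The concern.** The plan treats sun as important enough to adjust for, but the score as described measures what patients do outdoors, not how strong the sun is at that time of year. The same score in December and in June need not mean the same vitamin D production.

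Baseline adjustment fixes the starting level, not the direction of travel. If 25(OH)D has a seasonal cycle, two untreated patients with the same baseline, one entering in spring and one in autumn, are expected to drift in opposite directions over 8 weeks. Without a season term, that drift goes into the residual.

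What is at stake is precision. The vitamin D arms should separate from placebo either way. The loss is felt in the width of the intervals, and most in the pairwise 25(OH)D contrasts where little difference is expected: co-supplementation against vitamin D alone, and omega-3 alone against placebo.

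**Working it through.** **From the article.** Recruitment: 30 April 2018 to 30 April 2019 is 365 days, plus 15 days to 15 May, giving 380. Head count: 20/(1 − 0.20) = 25 per group and 4 × 25 = 100, so about 80 completers. There is no stated figure for 25(OH)D to reproduce.

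**Assumed, because the article gives none of it.** Non-seasonal 25(OH)D SD 8 ng/ml (variance 64); baseline-to-end correlation 0.6; a sinusoidal seasonal mean with half-range A (mean to peak) of 3, 4 or 5 ng/ml, equal in all arms; even entry over the year.

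**Drift over 8 weeks.** The phase shift is 2π × 56/365 = 0.964 rad, with cosine 0.570. The largest drift is 2A·sin(0.482) = 0.927A, that is 2.8, 3.7 or 4.6 ng/ml up or down. Its SD across entry dates is 0.927A/√2 = 0.656A, or 2.0, 2.6 and 3.3 ng/ml. The 25(OH)D change in the second objective carries this component too.

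**Residual variance after baseline, no season term.** Let S = A²/2, V = 64 + S and C = 0.6 × 64 + 0.570·S. The residual is V − C²/V. With season in the model it is 64 × (1 − 0.36) = 40.96.

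| A | S | V | C | Residual without season | With season | Ratio |
|---|---|---|---|---|---|---|
| 3 | 4.5 | 68.5 | 40.97 | 44.00 | 40.96 | 0.931 |
| 4 | 8 | 72 | 42.96 | 46.37 | 40.96 | 0.883 |
| 5 | 12.5 | 76.5 | 45.53 | 49.40 | 40.96 | 0.829 |

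**Credit for the sun score.** Let a baseline sun score (variance 1) correlate 0.8 with the seasonal curve. At A = 5 its covariance with baseline 25(OH)D is 0.8 × √12.5 = 2.828, and with the end value 2.828 × 0.570 = 1.613. Conditional on the score, the baseline variance is 76.5 − 8.0 = 68.5, the end variance 76.5 − 2.6 = 73.9, and the covariance 45.53 − 4.56 = 40.97. The residual is 73.9 − 40.97²/68.5 = 49.4, practically unchanged. In this model the score repeats the seasonal level that baseline already carries and says little about direction.

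**Cost of two extra terms.** With N = 80, four arms and q covariates, the contrast variance carries a factor of about 1 + q/(N − 5 − q). For q = 2 (baseline, sun score) that is 1 + 2/73 = 1.027; for q = 4 it is 1 + 4/71 = 1.056. The penalty ratio is 1.028.

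**Net variance reduction.** A = 3: 1 − 0.931 × 1.028 = 4%. A = 4: 1 − 0.883 × 1.028 = 9%. A = 5: 1 − 0.829 × 1.028 = 15%. As √0.96 = 0.98 and √0.85 = 0.92, intervals become about 2 to 8% narrower. Simulated trials agree to within a couple of percentage points. At A = 2 the net gain is about 1% or less.

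**Sensitivity.** With between-person SD 6 and within-person SD 3 (variance 45, correlation 36/45 = 0.8), simulations that also apply the entry limit of 30 ng/ml and include a sun score give reductions of 9–12% at A = 3 and 23–34% at A = 5 for omega-3 alone against placebo. Contrasts involving a vitamin D arm gain less if response to the supplement varies between patients: with an assumed response SD of 6, co-supplementation against placebo gains 1–8% and 13–19%.

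**The case against.** **The covariate list is open.** It is introduced as examples, in a condensed article, and a full list may sit in an analysis plan not shown. This stands. A reader might infer that the ANCOVA excludes season; the article supports only that season is not named. What remains is that the one sun-related covariate it chose to name has no calendar item among its listed components.

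**The questionnaire may capture season.** The article summarises a cited instrument in one sentence, so it may record more than is described. Time outdoors and skin exposed plausibly vary with season. The score is also taken at the end, and its change could reflect the direction of drift; the article does not say which measurement enters the model. This may shrink the gain, and it limits the point to the score as described.

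**Randomization protects the comparison.** This also stands. A reader might infer that seasonal imbalance could produce false differences more often than the nominal 5%. It does not: season is independent of arm in expectation, and the standard error already allows for chance imbalance. Simulating omega-3 alone against placebo without a season term gave type I error of 3.1%, 5.6% and 4.0% at half-ranges of 3, 5 and 8 ng/ml (1,500 trials each), with no sign of inflation. Counting how many patients in each arm enrolled in the first half of recruitment would not strengthen the case, because that half mixes spring and autumn entrants, who drift in opposite directions.

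**The consequence is small.** The sample size rests on TNF-α, so the stated number and power are unaffected, and no stated hypothesis singles out an effect of omega-3 on 25(OH)D. This is why the point is minor.

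**Conclusion.** The point holds as a minor precision suggestion, not as an error in the plan. The article establishes a 380-day recruitment period, a sun score described without a time-of-year item, and no mention of season among the example covariates for an outcome named first in the primary objective.

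The size cannot be derived from the article. Under the stated assumptions (SD 8, correlation 0.6, half-range 3 to 5 ng/ml, 20 completers per arm), naming season lowers the variance of a 25(OH)D contrast by roughly 4 to 15%. It would be more with smaller within-person noise or a larger amplitude, and negligible if the amplitude is small.

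The second objective deserves the same term for a different reason. Relating 25(OH)D change to other variables is not a randomized comparison, so a seasonal component shared with another variable could contribute to an association there. Whether any other variable here is seasonal is not known from the article.

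**What to change.** In the ANCOVA sentence of the Statistical analysis section, name season of the baseline blood sample as a prespecified covariate for serum 25(OH)D, before unblinding. Use either the sine and cosine of the sampling date or a four-level season factor. Keep the sun score; season is added beside it. Use the same term when 25(OH)D change is related to other variables under the second objective, since changing the ANCOVA sentence alone would not reach that analysis.

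The cost is 2 degrees of freedom for the sine and cosine pair, or 3 for the factor, out of about 75 (80 completers less four arm means and baseline). The date precedes treatment and cannot be affected by it. No new data should be needed, provided that sampling dates are kept with the blood samples. Sample size and trial conduct do not change.

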### Sample size

The number of participants was calculated according to the alterations in TNF-α between the control and co-supplementation groups and based on the study conducted by Mohammadzadeh et al. [25]. It was calculated with the use of fixed factor levels model (determining sample size for analysis of variance) [26] and considering sigma (standard deviation of TNF-α) of 1.25, 90% power, α of 0.05, resulting in 20 patients for each group. To allow for attrition, 25 patients will be recruited for each group. Collectively, a sample of 100 patients with stage II or III CRC will be enrolled.

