### Randomization and blinding

The randomization assignment will be performed using computer-generated random numbers. The 100 participants who meet the criteria will be randomly allocated into four groups: 1) a 50,000 IU vitamin D soft gel (weekly) plus 2 omega-3 fatty acid capsules (daily), each capsule containing 330 mg omega-3 fatty acid; 2) a 50,000 IU vitamin D soft gel (weekly) plus 2 omega-3 fatty acid placebo (daily); 3) a vitamin D placebo (weekly) plus 2 omega-3 fatty acid capsules (each capsule containing 330 mg omega-3 fatty acid); and 4) a vitamin D placebo (weekly) plus 2 omega-3 fatty acid placebo (daily). Each omega-3 fatty acid capsule (MorDHA VISION, Minami Nutrition, Belgium) contains 54 mg EPA, 250 mg DHA, and 26 mg of other omega-3 fatty acids. The 50,000 IU vitamin D soft gels are supplied by Zahravi, Iran. The vitamin D and omega-3 fatty acid placebo contain oral paraffin and corn oil, respectively, are supplied by Zahravi, Iran, and are carefully matched in appearance with vitamin D and omega-3 fatty acid soft gels. Patients will receive verbal and written counseling on how to consume the capsules. Compliance will be evaluated by capsule count every 2 weeks. The supplementation will begin before the first session of chemotherapy.

For blinding, a person not involved in the study protocol will create the randomization list, assigning participants to the vitamin D, omega-3, co-supplementation, or placebo group. Vitamin D, omega-3, and placebo tablets will be placed into unlabeled identical containers. The study leader will label these containers with participant numbers using the randomization list. All investigators and participants will be blinded to the random assignments.

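### Single-step Bonferroni for the six pairwise comparisons is valid but gives up power that a step-down test would keep at the same 5% family-wise error per outcome

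*Protocol article*

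**What the plan says.** Under Randomization and blinding: "The 100 participants who meet the criteria will be randomly allocated into four groups". Four arms give 4 × 3 / 2 = 6 possible pairs.

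Under Statistical analysis, the overall test comes first: "Analysis of covariance (ANCOVA) will be used to identify any differences between the four groups at the end of study", adjusted for baseline and covariates. The pairwise step is one sentence: "Bonferroni will be used to pairwise comparisons for the values after the intervention". It names no subset of pairs and no step-down version, and it does not make the pairwise tests depend on the four-group test.

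Under Sample size, the trial is sized on "alterations in TNF-α between the control and co-supplementation groups", using a "fixed factor levels model (determining sample size for analysis of variance") and "considering sigma (standard deviation of TNF-α) of 1.25, 90% power, α of 0.05, resulting in 20 patients for each group". No difference between group means is given.

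**The concern.** Plain Bonferroni holds every pair to 0.05/6, as though all six null hypotheses could still be true however strong the evidence against some of them. A step-down procedure relaxes the level as pairs are rejected. The plan also already contains a four-group test at 0.05. Once that test has rejected, at most three of the six pairwise nulls can be true, so dividing by six is stricter than 5% control requires.

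What is at stake is power for the smaller contrasts: one supplement against placebo, and co-supplementation against one supplement. With 20 patients per arm these are the weakest comparisons in the plan, and they lose most from an unnecessarily strict level.

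**Working it through.** **Inputs from the protocol article.** Four arms, α = 0.05, SD 1.25, 90% power, 20 per arm before attrition. Error degrees of freedom are 4 × (20 − 1) = 76, ignoring the few lost to covariates. The effect size is not stated, so effects of 0.8, 1.0 and 1.25 SD are assumed.

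**The plan's own figure.** The 20 per arm cannot be reproduced from the stated inputs, because the range of group means is missing. In the noncentral-F calculation for four groups, with noncentrality n × (range/SD)² / 2, an assumed range of 1.25 SD gives n = 20 with 91.4% power. Exactly 90% at n = 20 needs a range of about 1.22 SD. The attrition step reproduces: 20 / 0.8 = 25, and 4 × 25 = 100.

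**Logic of the step-down.**
1. Among four means, the number of true pairwise nulls can only be 6, 3, 2, 1 or 0.
2. If all six are true, a false pairwise claim under the gated procedure first needs a false rejection by the F test, which has probability at most 0.05.
3. Otherwise at most three are true, and 3 × 0.05/3 = 0.05.
4. The gated Shaffer-Holm levels are therefore 0.05/3 for the four smallest p-values, then 0.05/2, then 0.05.
5. Holm needs no gate. It uses 0.05/6, 0.05/5, and so on down to 0.05, and it rejects everything Bonferroni rejects.

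**Critical values, 76 df, two-sided.** At 0.05/6, |t| = 2.709. At 0.05/3, |t| = 2.448.

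**Power per true pair.** Simulation with 20 per arm, common SD and pooled-variance t tests:

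| Assumed pattern | Bonferroni | Holm | F-gated Shaffer-Holm |
|---|---|---|---|
| One arm differs by 0.8 SD | 43% | 46% | 51% |
| One arm differs by 1.0 SD | 67% | 70% | 75% |
| One supplement active at 1.0 SD | 67% | 73% | 76% |
| Additive, 0.8 SD total: single vs placebo | 8% | 9% | 12% |
| Additive, 0.8 SD total: co-supplementation vs placebo | 43.5% | 44% | 47% |
| Additive, 1.25 SD total: single vs placebo | 24% | 28% | 33% |
| Additive, 1.25 SD total: co-supplementation vs placebo | 89% | 89% | 90% |

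**Family-wise error for one outcome.**

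| Pattern | Bonferroni | Holm | F-gated Shaffer-Holm |
|---|---|---|---|
| All arms equal | 4.1% | 4.1% | 4.8% |
| Three equal, one far away | 2.3% | 4.4% | 4.4% |
| Two equal pairs far apart | 1.7% | 4.9% | 4.9% |

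The largest value in any pattern tried is 4.9%. Testing every pair at 0.05/3 without the F gate gives 7.7% when all arms are equal.

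**Cost of the gate.** Trials in which Bonferroni declares some pair but the F test does not reject: 0.6% in the additive 1.25 SD pattern, and 1.2% in the additive 0.8 SD pattern. Net power per true pair still rose in every pattern above.

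**The case against.** The strongest reply is that nothing here is wrong. Bonferroni after a four-group ANCOVA is conventional and controls the family-wise error. It also gives simultaneous confidence intervals that agree with the tests, which is a legitimate reason to prefer it in a small biomarker trial. That stands, and it is why this is only a suggestion.

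Four further points have force:
- The six pairs and the level 0.05/6 are inferred. The article is a condensed text, and the full plan may limit the pairs or already gate them on the ANCOVA.
- The contrast on which the trial was sized gains only about one percentage point in the additive 1.25 SD pattern, and single versus placebo remains badly underpowered at 33%.
- In a factorial design, the question of which component works is more naturally answered by main effects and the interaction than by six pairs of 20 against 20. This does not change the comparison of methods for the pairwise tests that the plan does state.
- Error control here is per outcome. The Objectives section lists several outcomes together as primary, and neither procedure deals with that.

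A reader might infer that the plan inflates error, that real differences are lost for no return, or that 0.05/3 can simply replace 0.05/6. None of these is supported. Bonferroni is conservative, it buys matching intervals, and 0.05/3 is valid only behind an F gate that the article does not state. A reader might also turn the change in critical value into a saving in patients, (2.709 + 0.842)² / (2.448 + 0.842)² = 1.165, or about 16%. That ratio ignores the gate and overstates the gain for the sized contrast.

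**Conclusion.** This is a cheap improvement, not an error. Read as written, the plan uses a valid procedure that is less powerful than two alternatives with the same 5% family-wise control per outcome. At assumed effects of 1.0 SD the gain per true pair is about 3 to 6 percentage points with Holm and 8 to 9 with the gated step-down. For half-range contrasts in the additive 1.25 SD pattern it is about 4 and 9 points. For co-supplementation versus placebo in that pattern it is 0 to 1 point.

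The conclusion rests on all six pairs being tested, on 20 completers per arm with a common SD, and on assumed effect sizes, since the protocol gives none. The ordering of the three methods held in every assumed pattern tabulated, apart from a tie between Bonferroni and Holm, after rounding, for the largest contrast. The size of the gain depends on the pattern.

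**What to change.** Replace the Bonferroni sentence with one of these, fixed in writing before unblinding:

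- *For each outcome, the six pairwise adjusted differences from the ANCOVA model will be tested by Holm's procedure.*
- For more power: *For each outcome, the six pairwise adjusted differences from the ANCOVA model will be tested only if the four-group F test for that outcome is significant at 0.05, by the Shaffer-Holm step-down (0.05/3 for the four smallest p-values, then 0.05/2, then 0.05).*

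The F-test condition must appear in the second version. In either case, report 95% confidence intervals labelled as unadjusted beside the adjusted p-values, because an interval may exclude zero for a pair that is not declared different.

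The change needs no extra data or patients. It gives up simultaneous intervals taken directly from the test. With the gate, an occasional pair that Bonferroni would have declared is lost (0.6% to 1.2% of trials in the additive patterns shown). If matching simultaneous intervals matter more to the investigators than power, keeping Bonferroni is defensible and one sentence saying so is enough. Multiplicity across outcomes needs its own rule whichever version is chosen.

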## Discussion

Vitamin D metabolites exert significant anti-neoplastic effects in preclinical models. In clinical trials, the effect of vitamin D has been reported in various types of cancer. A low vitamin D level and/or activity is related to an increased risk of cancer and a more aggressive tumor growth, while high activity of this pathway leads to anti-tumoral impacts [2]. Moreover, some meta-analyses looking at vitamin D and cancer incidence and mortality reported that vitamin D supplementation decreased the risk of cancer mortality [23, 24].

Previous investigations in health subjects have reported a relationship between polyunsaturated long chain n-3 fatty acids and lower levels of pro-inflammatory biomarkers and the tumor marker CEA, supporting the concept that n-3 fatty acids may be useful in patients affected by diseases described by active inflammation.

Inflammation is a common feature of cancer. The presence and extent of a chronic systemic inflammatory response may lead to progressive nutritional decline. Therefore, a specific nutritional intervention resulting in a decrease in the inflammatory state, and consequently ameliorating nutritional status, could be a successful strategy for CRC therapy.

Based on the results of previous studies, it seems that both vitamin D and omega-3 fatty acids may provide a new complementary treatment by decreasing inflammatory biomarkers and resistance to cancer treatment in patients with CRC. The question remains whether vitamin D and omega-3 fatty acids co-supplementation would actually be useful after diagnosis of CRC. So, the aim of this study is to investigate the effects of vitamin D and omega-3 fatty acids co-supplementation on inflammatory biomarkers, tumor marker CEA, and nutritional status in patients with CRC.

